## Abstract

**Background:**

Lower extremity trauma during earthquakes accounts for the largest burden of disaster-related injuries. Insufficient pain management is common in resource-limited disaster settings, and regional anesthesia (RA) may reduce pain in injured patients beyond current standards of care. To date, no controlled trials have been conducted to evaluate the use of RA for pain management in a disaster setting.

**Methods/design:**

The Regional Anesthesia for Painful Injuries after Disasters (RAPID) study aims to evaluate whether regional anesthesia (RA), either with or without ultrasound (US) guidance, can reduce pain from earthquake-related lower limb injuries in a disaster setting. The proposed study is a blinded, randomized controlled equivalence trial among earthquake victims with serious lower extremity injuries in a resource-limited setting. After obtaining informed consent, study participants will be randomized in a 1:1:1 allocation to either: standard care (parenteral morphine at 0.1 mg/kg); standard care plus a landmark-guided fascia iliaca compartment block (FICB); or standard care plus an US-guided femoral nerve block. General practice humanitarian response providers who have undergone a focused training in RA will perform nerve blocks with 20 ml 0.5 % levobupivacaine. US sham activities will be used in the standard care and FICB arms and a normal saline injection will be given to the control group to blind both participants and nonresearch team providers. The primary outcome measure will be the summed pain intensity difference calculated using a standard 11-point Numerical Rating Scale reported by patients over 24 h of follow-up. Secondary outcome measures will include overall analgesic requirements, adverse events, and participant satisfaction.

**Discussion:**

Given the high burden of lower extremity injuries in the aftermath of earthquakes and the currently limited treatment options, research into adjuvant interventions for pain management of these injuries is necessary. While anecdotal reports on the use of RA for patients injured during earthquakes exist, no controlled studies have been undertaken. If demonstrated to be effective in a disaster setting, RA has the potential to significantly assist in reducing both acute suffering and long-term complications for survivors of earthquake trauma.

**Trial registration:**

ClinicalTrials.gov (NCT02698228), registered on 16 February 2016.

## Background

Between 1994 and 2013, approximately 7000 natural disasters were reported globally, affecting more than 200 million people and accounting for over one million deaths. Earthquakes, and their resultant morbidity and mortality, have increased over time due to population growth and increasing urbanization. Given these trends, earthquakes now account for the largest burden of injury among all types of geophysical disasters [1, 2].

Epidemiologic studies from multiple settings consistently show that trauma sustained during earthquakes predominantly injures the extremities, with the lower limbs most commonly affected [3–6]. The high frequency of lower limb trauma during earthquakes makes interventions directed at the management of these injuries critical [7].

Inadequate pain management due to oligoanalgesia is common in nondisaster acute care treatment [8–10]. In the emergency response phase to a natural disaster, where resources are often constrained, oligoanalgesia is even more common [11–13]. Standard pain management in disaster settings for severe lower limb injuries includes intramuscular or intravenous injections of narcotic pain medications, with morphine being the recommended agent [14, 15]. However, narcotic medications may be unavailable in low-income settings, and patients with trauma may have clinical instability making narcotic medications less safe to use; both factors can be barriers to appropriate pain treatment for earthquake victims [11, 16]. Subsequently, insufficient pain management can potentiate both short-term and long-term sequelae, including immunosuppression, thrombotic complications, post-traumatic stress disorders, and chronic pain syndromes, all of which may further increase the morbidity associated with index injuries [12, 17].

Regional anesthesia (RA) has the potential to address the suboptimal pain management that often occurs after earthquakes. RA involves injecting local anesthetic medications around a nerve in order to block sensation to a specific anatomic region [18]. Prior studies have demonstrated that RA to achieve femoral nerve blockade is a rapid and safe method for pain management of lower extremity trauma [19–23]. Hospital-based studies have found RA to be more effective at reducing pain as compared to narcotics alone in patients with limb injuries. However, nearly all studies on RA have been conducted in high-resource settings, using specially trained proceduralists, and have enrolled only patients with simple hip or femoral fractures [24–26]. This population is not representative of earthquake victims, who more frequently have complex injuries including multiple, open fractures and crush mechanisms, thereby limiting the generalizability of these RA findings to disaster response settings.

RA can be achieved using either anatomic landmark or ultrasound (US) guidance. Both the anatomically guided fascia iliaca compartment block (FICB) and the US-guided femoral nerve block (FNB) primarily target the femoral nerve, and with injection of an anesthetic agent can provide analgesia for much of the lower extremity [18]. A review article concluded that US-guided nerve blocks have the potential to greatly improve pain control in disaster settings [17]. However, the published literature on the use of US-guided RA in disasters is limited, and no controlled trials have evaluated the effectiveness of RA in a disaster context or resource-limited setting. A few studies have suggested that local anesthetic injection using US may reduce complication rates compared to anatomic landmark-guided injection [27]. However, a systematic review found no evidence that US-guided RA was more effective than the use of landmark-guided injections [27]. Furthermore, the anatomic method does not require investment in costly US equipment, which may be important in a resource-limited or disaster setting.

There are anecdotal reports of the use of both anatomic landmark- and US-guided RA for the treatment of earthquake-related injuries, suggesting the feasibility of these modalities in a disaster setting. However, there have been no randomized controlled trials (RCTs) conducted to evaluate the effectiveness, safety, or acceptability of RA in the aftermath of a major earthquake [13, 28, 29]. Given the burden of disease, consistent patterns of injuries, and inadequate pain treatment documented in earthquake settings, interventions to address this substantial global health burden are needed. A rigorous assessment of the use of RA techniques to address pain management in disaster settings would be useful to inform treatment protocols. To address this current deficit, the Regional Anesthesia for Painful Injuries after Disasters (RAPID) study aims to enroll patients in the aftermath of a major earthquake to determine whether regional anesthesia, either with or without ultrasound guidance, can reduce suffering from lower limb injuries, the most common earthquake-related injury, as compared to current standard of care for pain control in these settings.

## Methods

### Design

The RAPID study will be conducted in the aftermath of a major earthquake to which a Médecins Sans Frontières (MSF) field hospital is deployed at the request of the local Ministry of Health (MoH). The study design is a blinded RCT using an equivalence design. After obtaining informed consent, earthquake victims with serious lower extremity injuries will be randomized to one of three study arms. Eligible participants will be randomized in a 1:1:1 allocation ratio to either: standard care (defined below); standard care plus an anatomic landmark-guided FICB; or standard care plus an US-guided FNB. The structure of the study is illustrated in Fig. 1.

**Fig. 1 Fig1:**
[figure not shown]
Study flow diagram. Abbreviations: *MSF* Médecins Sans Frontières

### Aims

The goal of the RAPID study is to transform the way that serious injuries are managed after earthquakes and other disasters by introducing a cost-effective and anatomically appropriate method for pain control. The trial will enroll patients in the aftermath of a major earthquake to determine whether RA, either with or without US-guidance, can reduce suffering from lower limb injuries, as compared to current standard of care for pain control in these settings. The study will also evaluate if a brief, focused training for international and local generalist health care providers in RA is sufficient for them to gain competence in the RA procedures.

### Setting

As natural disasters can occur anywhere in the world, the specific geographic location for the RAPID study is not predetermined. Earthquakes occur with greater frequency in Asia and in the Americas, accounting for 55 % and 21 % of events over the preceding four decades, respectively [1]. As such, these are the most likely geographic settings for the trial.

The RAPID study will be restricted to low or middle-income countries (LMICs) as defined by the World Bank classification system [30]. As 70 % of the nations with the largest number of major earthquakes over the past 40 years are classified as LMICs, a resource-constrained setting will enhance the generalizability of the findings to venues with a higher future probability for such events [1]. Additionally, trial activities will take place in an MSF field hospital, which would only be deployed for a major disaster in a LMIC at the request of the local MoH.

In addition, this trial will only be conducted after an earthquake that meets at least one of the four criteria for a major disaster established by the Center for Research on the Epidemiology of Disasters (CRED): ten or more people reported killed, 100 or more people reported affected, a declaration of a state of emergency, and/or a call for international assistance [31]. The decision as to whether the earthquake meets these criteria will be made within 24 h of the event, to allow for trial commencement within 72–96 h of the event (Fig. 2).

**Fig. 2 Fig2:**

Study timeline

### Outcome measures

The primary outcome measure will be the summed pain intensity difference (SPID), a commonly used measure to assess efficacy of various pain management interventions [25, 32]. While the SPID has not been previously validated in a post-earthquake setting, it has been used in a variety of clinical settings around the world. SPID measures pain over time and controls for both cultural and individual differences in pain perception and expression. To calculate the SPID, participants will be asked to estimate their pain using a standard 11-point Numerical Rating Scale (NRS) at baseline (prior to treatment) and at set time points over the subsequent 24 h of follow-up (Fig. 3). The SPID will be calculated as the area under the curve describing the difference between current and baseline pain intensity at each time point.

**Fig. 3 Fig3:**
[figure not shown]
Numerical Rating Scale

Secondary outcome measures will include analgesic requirements, adverse events and patient satisfaction. Analgesic requirements will be recorded as the total amount of analgesic medication received during the full 24 h of patient follow-up. Adverse events (defined as any untoward medical occurrences in subjects receiving the investigational therapy) and serious adverse events (defined as any potentially life-threatening or disabling adverse events) will be monitored and recorded through structured reporting. Patient satisfaction with their overall pain management will be assessed via standardized questionnaires using Likert scales [33, 34].

### Study population

#### Screening

The study population will be comprised of those injured in association with the earthquake who present for care of lower limb injuries at the MSF field hospital. Study personnel will continuously screen all patients presenting to the field hospital until the sample size is reached. Patients meeting all inclusion criteria and no exclusion criteria will be eligible for enrollment.

#### Inclusion/exclusion criteria

The RAPID study will include adult patients (18 years or older) presenting to the MSF field hospital with one or more lower limb injuries. The trial will exclude patients with multisystem trauma, severe respiratory distress, hypotension, altered mental status, active infection at the sight of injection, known current pregnancy, and those who are unable to provide informed consent. Patients with known allergies to local anesthetic agents or narcotic pain medication, those receiving antithrombotic therapy or with a preexisting coagulopathy, and those likely to receive regional anesthesia for alternative reasons within 2 h of screening will also be excluded.

### Informed consent

Study personnel, in conjunction with local translators, will obtain informed consent from all participants prior to enrollment. Since many study subjects may be illiterate, an informed consent script will be utilized that will be read aloud to them and translated into the local language. Subjects will then be able to consent via either a signature or a thumbprint on a Written Consent Form, based on their level of literacy.

### Randomization and blinding

Randomization will occur immediately following informed consent attainment. Study subjects will be individually allocated in a 1:1:1 parallel format into three distinct study arms via blocked randomization with six subjects per block. Allocation will be achieved using sealed envelopes containing computer-generated and preprinted randomization assignments with unique patient identification numbers.

The enrolled participants and the treating health care teams will be blinded to the patient’s allocation arm through uniform exposure to US scanning and injection procedures as outlined below. Only the research team proceduralist delivering the injection will know the intervention received by the patient.

### Allocation arms

The RAPID trial will have three allocation arms (Fig. 1). The first arm will serve as the control group in which participants will receive a standard parenteral injection of 0.1 mg/kg of morphine either intravenously or intramuscularly. Additionally, 5 ml of 0.9 % normal saline (placebo) will be injected into the subcutaneous tissue of the anterior proximal thigh by the proceduralist. Concurrent with the normal saline injection, the US probe will be placed on the patient’s thigh in close proximity to the injection site in order to facilitate blinding.

The second arm will receive the standard 0.1 mg/kg of morphine followed by an injection of 20 ml 0.5 % levobupivacaine into the fascia iliaca compartment. In this arm, the FICB will be performed using standard anatomic landmarks to guide the injection [35]. To achieve blinding during the anesthetic injection, the US probe will also be placed on the skin of the thigh in close proximity to the injection.

The third arm of the RAPID trial will involve treatment with US-guided FNB. In this arm, enrolled participants will receive the standard 0.1 mg/kg of morphine followed by an injection of 20 ml 0.5 % levobupivacaine around their femoral nerve under direct US-guidance [35].

All patients enrolled in the study, regardless of treatment arm, will continue to receive standard care for pain based on the discretion of their treating health care providers in the field hospital. These providers will not be a member of the RAPID research team and will be blinded to the patient’s randomization arm. Enrollment in the study will not be allowed to delay any additional treatments or interventions deemed necessary by the treating team.

### Research personnel training and deployment

Prior to initiation of the trial, and preceding the earthquake event, a cohort of MSF nurses and physicians will be trained in study procedures via a structured interactive course. These practitioners will make up the international portion of the RAPID research team, responsible for data collection and procedural activities. The training will cover all study procedures, including both anatomic landmark- and US-guided femoral nerve blockade for RA [18, 36]. For each trainee, minimum competence will be assessed using a didactic knowledge test and assessment of procedural abilities through direct observation using phantom training models. All research team members will participate in an additional and mandatory Good Clinical Practice (GCP) training.

Within 72–96 h of the earthquake event, members of the RAPID research team will be deployed alongside the MSF response team and field hospital to the site of the disaster. The research team will be divided into shifts, to facilitate 24-h enrollment; each shift will include, at minimum, one data collector, a proceduralist, and a local translator.

As outlined in Fig. 2, study coordinators will also hold an onsite procedural training for locally recruited health care providers, who will take over as the RAPID proceduralists during the latter half of the study. These providers will be trained and assessed onsite using the same methods as the international portion of the research team.

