### Data collection

Data collection time points are outlined in Fig. 1. Study personnel will assess the subject’s pain score and vital signs at baseline and again at eight predetermined intervals using the 11-point NRS (Fig. 3). Adverse events will be monitored throughout the follow-up period. Additionally, subject satisfaction with their care and total amount of required analgesic medications will be assessed at the conclusion of the study for each participant. Baseline demographic characteristics and information on mechanism of injuries will also be gathered at the time of enrollment. As the population being evaluated will be followed-up for only 24 h at a single study site and will have substantial physical trauma, it is likely that losses to follow-up through discharge prior to 24 h or patients leaving against medical advice will be minimal.

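### A fixed, published block size of six at a single site lets a well-informed team member deduce some upcoming allocations; the block sizes should vary and be withheld

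*Protocol article*

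**What the plan says.** Under Randomization and blinding, patients are allocated individually in a 1:1:1 ratio "via blocked randomization with six subjects per block". Randomization follows consent directly, using sealed envelopes with preprinted assignments. Data collection refers to a single study site, and the Sample size section plans 207 participants.

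On who knows the arm, Randomization and blinding states: "The enrolled participants and the treating health care teams will be blinded to the patient’s allocation arm". It adds: "Only the research team proceduralist delivering the injection will know the intervention received by the patient". The abstract describes the sham procedures as intended "to blind both participants and nonresearch team providers". Under Data collection, the outcome assessor is named only by a general term: "Study personnel will assess the subject’s pain score and vital signs at baseline and again at eight predetermined intervals".

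On staffing, Research personnel training and deployment says of the trained cohort: "These practitioners will make up the international portion of the RAPID research team, responsible for data collection and procedural activities". The next paragraph gives the roster: "each shift will include, at minimum, one data collector, a proceduralist, and a local translator". Trial status reports 12 trained study personnel. Locally recruited providers take over as proceduralists in the latter half of the study.

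**The concern.** Blocking keeps the arms balanced, but it makes the end of each block predictable to anyone who knows the block length and has seen its earlier places. Three features combine here. The length never changes and is in print. A single site implies one allocation sequence. And a team of limited size includes proceduralists who cannot be blinded to what they inject.

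At stake is allocation concealment, which is separate from blinding after allocation. If someone involved in recruitment could foresee the next arm, the approach to a particular patient, or its timing, could come to depend on that arm. The Discussion justifies randomization by the risk that more seriously injured patients would preferentially receive regional anesthesia. Foreseeable allocation lets a weaker form of that same confounding back in. The direction of any resulting bias cannot be stated in advance.

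A smaller matter is clarity. The two descriptions of who is blinded differ in scope, and neither names the data collector, although the primary outcome is built from pain scores taken by study staff.

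**Working it through.** The article states no predictability figure to reproduce, so the check counts outcomes exactly.

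**Inputs.** Block size 6 and ratio 1:1:1 (Randomization and blinding), hence 6/3 = 2 places per arm. Total 3 × 69 = 207 (Sample size). 207 = 34 × 6 + 3, that is, 34 full blocks and half of another. Distinct block orders: 6!/(2!·2!·2!) = 90.

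**Next arm certain.** The observer knows the block size and every earlier allocation in the block.
- Place 6: always certain, probability 1.
- Place 5: certain when the last two places hold the same arm: 3 arms × 6 orders of the other four = 18 of 90 = 1/5.
- Places 1 to 4: never, since at least three places remain and no arm has more than two.
- Share: (1 + 1/5)/6 = 20 %. Over the trial: 34 × 1.2 = 40.8, and the final half block adds 0, so about 41 of 207.

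**Control versus regional anesthesia certain.** With *m* places left, the answer is certain if no control place remains or if control fills all of them. The two control places can fall in C(6,2) = 15 ways.

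| Place | *m* | Favourable / 15 |
|---|---|---|
| 6 | 1 | 15 |
| 5 | 2 | 6 + 1 = 7 |
| 4 | 3 | 3 |
| 3 | 4 | 1 |
| 1, 2 | 6, 5 | 0 |

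Share: (15 + 7 + 3 + 1)/15/6 = 28.9 %. Over the trial: 34 × 26/15 + 1/15 = 59.0 of 207. The simple product 0.289 × 207 gives 59.8.

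**Best guess rather than certainty.** By place, the chance of naming the right arm is 0.333, 0.400, 0.500, 0.533, 0.600 and 1.000. The mean is 56.1 %, against 33.3 % by chance. For control versus regional anesthesia the mean is 74.4 %, against 66.7 % for always guessing regional anesthesia.

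**If one earlier allocation per block is unknown.**
- Exact arm: when the missed place is among 1 to 4, only place 6 can be certain, with probability 1/5, giving 0.2/6 = 3.3 %. When place 5 is the one missed, (0.2 + 0.2)/6 = 6.7 %.
- Control versus regional anesthesia: from (7 + 3 + 1)/15/6 = 12.2 % (place 1 or 2 missed) to (7 + 7 + 3 + 1)/15/6 = 20.0 % (place 5 missed).

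**Would a larger fixed block do?** A known block of nine still leaves 14.3 % of arms certain and a best-guess accuracy of 53.2 %. Length alone helps little.

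**Blinding statements side by side.** The sentence confining knowledge to the proceduralist implies that the data collector is blinded. The list of blinded parties in the same section, and the abstract, cover only participants and non-research providers. These statements are compatible but not equal in scope. The distinction has practical content because the injections look different: 5 ml under the skin in the control arm, 20 ml in the other two (Allocation arms).

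**The case against.** A reader might infer from the cohort description that the same practitioners inject patients and then collect their pain scores. The article does not support this. That sentence describes the cohort as a whole, and the roster in the next paragraph lists a data collector and a proceduralist separately on every shift. The randomization section also limits knowledge of the arm to the person giving that injection. Rules on rostering across shifts, or on who may be present at the injection, are operational detail that an article may leave elsewhere, and Safety monitoring says the research methods will be set out in SOPs. Their absence here is no error. The pain score is also reported by patients who are themselves blinded.

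On the block size, the strongest reply is that no one is shown to hold all the information needed. Each proceduralist is said to know only the allocations he or she delivers, enrolment runs around the clock in shifts, and local providers later take over. Screening is continuous and covers all presenting patients. Screening and consent fall to study personnel, and no sentence gives the proceduralist control of enrolment.

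This stands as a limit on size, and it is why the percentages are ceilings and not expected effects. It does not remove the point. The article does not keep proceduralists out of recruitment either, and colleagues on one site can share what they know. Opening a sealed envelope after consent protects its contents, but not against someone who has counted the earlier ones.

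**Conclusion.** The point holds in a limited form. Fixed, published blocks of six at one site leave up to one allocation in five fully deducible, and up to 28.9 % deducible as control or regional anesthesia. Both figures assume an observer who knows the block size, where each block starts and every earlier allocation in it. They fall quickly as that knowledge becomes partial, and they are not estimates of bias in the SPID comparison. This is an avoidable weakness with a nearly free remedy, not a flaw that undermines the trial.

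On blinding, the article needs only a clarification: assessor blinding is implied in one place and not stated in another.

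**What to change.** **Main change.** Replace the fixed blocks of six by a computer-generated list with randomly varying block sizes in multiples of three. The sizes should be held by someone outside the field team and withheld from all field staff. The protocol can state that sizes vary without giving them. Withholding is essential, because a block of three recognised as such makes its last place certain, or one patient in three. Varying sizes do not reduce guessing to pure chance, but staff who cannot tell where a block ends can no longer find its last places simply by counting.

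**Cost.** A new list and new preprinted envelopes. Trial status says the study has yet to commence, so no allocated patient is affected. The downside is a slightly larger possible imbalance: if the largest block were nine, two arms could differ by at most three patients when recruitment stops. The present scheme can already differ by two, because 207 ends halfway through a block.

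**Clarification.** Align the abstract with Randomization and blinding by stating that each participant's outcomes are collected by someone who neither delivered nor observed that participant's injection. Each shift already includes both roles, so the cost is wording and slightly less flexible rostering.
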